### Ambulatory blood pressure monitoring

At Visit 1, and subsequently at Visit 5 and at final visit (Visit 7) an ambulatory blood pressure monitoring will be performed non-invasively over 24 h by an oscillometric validated device
[36,37]. Current Guidelines will be followed for proper recording performance
[38,39]. The monitoring cuff will be wrapped around the non-dominant arm and the patient will be asked to keep her/his arm still during the automatic blood pressure measurements. The device will be programmed to measure blood pressure every 15 min during the whole 24 h. Each recording will start in the morning, before 07:00 and 10:00, immediately after office blood pressure assessment. Patients will then be sent home, asked to resume normal life, and to come back 24 h later for removal of the device.

### Home blood pressure monitoring

The modality of self-blood pressure measurement at home has been detailed in the previous sections. In the HBPT group home blood pressure reports will be automatically transmitted to the Investigator every month for the first 12 weeks (from Visits 2 to 5). Based on these reports, the Investigator will be allowed to adjust drug treatment before the next visit or to schedule an extra study visit. Starting from Visit 5 until the end of the study (Visit 7), the patients randomized to HBPT will continue to self-measure blood pressure at home, but automatic transmission will be disabled and each patient will be asked to manually send blood pressure data the day immediately preceding the office visit at the Center. These home blood pressure measurements will be reviewed by the Investigator exclusively on Visits 6 and 7, and treatment adjusted accordingly.

### Psychological tests

With the aim to investigate the psychological impact of HBPT clinical psychologists will assess psychological dimensions at Visits 2, 5, and 7 by using the following standardized questionnaires: 

(1) SF-36: a generic tool for assessing the quality of life, aiming at quantifying the impact of disease on general health and on the psychological profile, for the determination of the most characteristic aspects affecting quality of life in relation to a standard reference population
[24]

(2) PGWBI: a tool for the assessment of psychological wellbeing
[25]

(3) BDI: this test can be considered as a standard reference among the self-assessment scales. A key feature of the scale is the precise definition of the criteria for quantification, since every item corresponds to a given level of severity. The scale is the most specific self-assessment tool for depression, exploring a narrow range of symptoms by excluding those related to anxiety
[26]

(4) LoC: this test measures the tendency to attribute the causes of behavior to internal or external conditions
[27,28]

(5) SEI: this test measures the degree of self-esteem of the patient
[29]

(6) IBQ: this test measures the disease perception
[30]

(7) COPE: the test is designed to be a measuring instrument capable of assessing the more subtle individual differences in coping. It is able to balance the general trend of the subject with the current response to the stressful situation. Due to its characteristics, this test is suitable for studies aiming at clarifying more thoroughly the possible influence of personality aspects on adaptation
[31]

In order to investigate the personality traits underlying the adherence behavior, clinical psychologists will also assess the following psychological dimensions only at Visit 2 by using the following standardized questionnaires:

(1) STAY: this test assesses the degree of trait anxiety severity
[32]

(2) TDP: the test evaluates the presence of the personality traits defined as being distressed
[33]

(3) TAP: the test evaluates the presence of type A personality traits
[34]

(4) TCI: a questionnaire for the self-evaluation of different personality characteristics, normal and abnormal, which is based on an interpersonal theory of personality
[35]

All psychological questionnaires used in the study are psychometrically validated and standardized on the Italian population.

### Statistical analysis

#### Primary outcome measures

The primary study endpoints are (1) the percentage of patients achieving daytime blood pressure normalization (systolic blood pressure <135 mmhg and diastolic blood pressure <85 mmhg) 24 weeks after randomization (visit 5); and (2) the percentage of patients achieving daytime blood pressure normalization after 48 weeks (visit 7).

The primary outcomes will be separately assessed for the HBPT and CM groups.

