**Methods/design:**

The purpose of this open label, parallel group, randomized, controlled study is to assess whether, in patients with high cardiovascular risk (treated or untreated essential arterial hypertension - both in the office and in ambulatory conditions over 24 h - and metabolic syndrome), long-term (48 weeks) blood pressure control is more effective when based on HBPT and on the feedback to patients by their doctor between visits, or when based exclusively on blood pressure determination during quarterly office visits (conventional management (CM)). A total of 252 patients will be enrolled and randomized to usual care (*n*=84) or HBPT (*n*=168). The primary study endpoint will be the rate of subjects achieving normal daytime ambulatory blood pressure targets (<135/85 mmHg) 24 weeks and 48 weeks after randomization. In addition, the study will assess the psychological determinants of adherence and persistence to drug therapy, through specific psychological tests administered during the course of the study. Other secondary study endpoints will be related to the impact of HBPT on additional clinical and economic outcomes (number of additional medical visits, direct costs of patient management, number of antihypertensive drugs prescribed, level of cardiovascular risk, degree of target organ damage and rate of cardiovascular events, regression of the metabolic syndrome).

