## Methods

### Study objectives

The study aims at investigating whether in high-risk patients with hypertension and metabolic syndrome, daytime ambulatory blood pressure control over 48 weeks is more effective when based on regular HBPT (intervention group), through monthly automated blood pressure teletransmission and feedback to the patient by the doctor, rather than when based only on periodic measurements made by doctors in their office during quarterly visits (conventional management (CM) control group). The main study endpoint will be the assessment and comparison of the rate of subjects achieving a daytime ambulatory blood pressure normalization (average daytime blood pressure <135/85 mmHg) in the two randomization groups (intervention *vs*. control).

The study will also assess the psychological determinants of adherence and persistence to drug therapy and the influence of HBPT on such psychological factors, as well as the impact of HBPT on additional clinical and economic outcomes. These will include the number of additional medical visits, direct costs of patient management, number of drugs or drug combinations used to achieve blood pressure control, the level of cardiovascular risk, the degree of target organ damage and frequency of cardiovascular events, and the regression of the metabolic syndrome.

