#### Sample size

The underlying study hypothesis is that the percentage of subjects achieving daytime blood pressure normalization will be 25% larger in the HBPT group. Using a two-tailed test with a 0.05 significance level and an 80% power, the estimated number of patients to be randomized is 252 (including a 25% drop-out rate), with 84 patients randomized to CM and 168 to HBPT.

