#### Planned statistical analyses

Analysis will be performed on patients valid for intention-to-treat, defined as all subjects with at least one visit during the randomized phase of the study and with valid ambulatory blood pressure recordings at baseline, after 24 and 48 weeks of follow-up even in the presence of protocol violations. A confirmatory analysis on the per-protocol (patients who have successfully completed the study without major protocol violations) is also foreseen.

The demographic and clinical characteristics of the two study groups will be compared at baseline by analysis of variance (continuous variables) or by Mantel-Haenszel Chi-square test (categorical variables), in order to verify the between-group homogeneity at randomization. The same tests will be used to compare primary and secondary study endpoints between the CM and HBPT groups. If deemed necessary, in addition to the univariate approaches, multivariate analysis methods will be used.

The type and frequency of drug-related adverse events will be reported for each randomization group. The absolute rate of adverse events will be compared between groups using the Chi-square test.

The minimum level of statistical significance will be set at *P* <0.05.

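### Two primary time points, weeks 24 and 48, are each tested at the full 0.05, and no alpha split, test order or both-required rule is stated

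*Protocol article*

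**What the plan says.** - Primary outcome measures numbers two endpoints. It opens "The primary study endpoints are (1) the percentage of patients achieving daytime blood pressure normalization" at week 24 (visit 5) and adds, as the second, "the percentage of patients achieving daytime blood pressure normalization after 48 weeks (visit 7"). Its remark on separate assessment concerns the two treatment groups and is not a multiplicity rule.
- The abstract gives one endpoint at two times: "rate of subjects achieving normal daytime ambulatory blood pressure targets (<135/85 mmHg) 24 weeks and 48 weeks after randomization". Study objectives says "The main study endpoint will be the assessment and comparison of the rate of subjects achieving a daytime ambulatory blood pressure normalization" and names no decisive time point.
- Planned statistical analyses: "The same tests will be used to compare primary and secondary study endpoints between the CM and HBPT groups", and "The minimum level of statistical significance will be set at *P* <0.05".
- Sample size: "Using a two-tailed test with a 0.05 significance level and an 80% power". It describes one comparison and does not say at which visit.

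None of these sections splits alpha, orders the two tests or says that both must be significant.

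**The concern.** The article gives the number of primary endpoints, the significance level for testing them and the alpha used for planning. These do not fit together: there are two primary tests at full alpha, and a sample size for one.

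The rule matters most when the two time points disagree, and the design makes disagreement plausible. According to Study design and Description of the intervention, automatic transmission runs for the first 24 weeks. After that, patients send their data manually before office visits. If the groups differ significantly at one time point only, the article does not say whether the trial succeeded. The trial is open label and, according to Trial status, follow-up was already under way. A rule chosen after the comparative results are known would not protect the 5% level.

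**Working it through.** **Inputs from the article.** Two primary endpoints; two-sided 0.05 for each; 80% planned power; 84 control and 168 telemonitoring patients; 25% drop-out. The analysis set requires valid ambulatory recordings at baseline, week 24 and week 48, so both tests use the same patients and should be positively correlated. The article does not give the correlation; I take 0 to 0.9.

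**The plan's own figure.** Evaluable patients: 84 × 0.75 = 63 and 168 × 0.75 = 126. The total of 252 cannot be derived, because no control rate is given and the 25% larger rate may be absolute or relative. Assuming 25 percentage points:

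- A 1:2 design at 0.05 needs at most 188 patients (208 with continuity correction) over the control rates tried.
- A 1:1 formula at a control rate of 37.5% gives 62 per arm; 62/0.75 rounds up to 83, and 83 + 166 = 249.
- A 1:2 design at 0.025 with continuity correction gives 248 at control rates of 35-40%.

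None of these equals 252. The section states 0.05, so the total is no evidence that two tests were allowed for. The error calculation below does not depend on it.

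**Error if either time point suffices.** With standard normal test statistics Z1 and Z2 of correlation ρ under no effect at either time:

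- Any false claim: 1 − P(|Z1| < 1.96, |Z2| < 1.96). At ρ = 0 this is 1 − 0.95² = 0.0975.
- False claim favouring telemonitoring: 1 − P(Z1 < 1.96, Z2 < 1.96). At ρ = 0 this is 1 − 0.975² = 0.0494.
- Both tests significant: 2 × 0.05 minus the first quantity.

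| ρ (assumed) | Either significant | Favouring telemonitoring | Both significant |
|---|---|---|---|
| 0 | 9.75% | 4.9% | 0.25% |
| 0.5 | 9.1% | 4.5% | 0.9% |
| 0.7 | 8.35% | 4.2% | 1.65% |
| 0.8 | 7.8% | 3.9% | 2.2% |
| 0.9 | 7.0% | 3.5% | 3.0% |

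A simulation of correlated binary outcomes, with 63 and 126 patients, the Pearson chi-square test and null rates of 30-50%, agrees. The either-significant error is 8.0-10.2% for within-patient correlations of 0 to 0.7, and 7.5-8.1% at 0.8.

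**Power cost of an alpha split.** Assume 25 percentage points and 63/126 evaluable. Power = Φ[(0.25 − z × SE0)/SE1], with SE0 from the pooled rate and SE1 from the separate rates. At a control rate of 37.5% against 62.5%:

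- Pooled rate (63 × 0.375 + 126 × 0.625)/189 = 0.5417; SE0 = 0.0769; SE1 = 0.0747.
- At 0.05 (z = 1.960): Φ(1.33) = 0.908.
- At 0.025 (z = 2.241): Φ(1.04) = 0.851.

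These are about the lowest values over control rates of 5-70%. On a relative reading of the 25%, with control rates of 20-45%, power would be only about 11-31% at 0.05 and 7-22% at 0.025.

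**The case against.** **Test order and alpha allocation are often left to the analysis plan, which is not shown.** This is fair, and such a plan may contain a rule. But the article does more than stay silent: it declares two primary endpoints, applies a flat 0.05 to them and plans for one test. That combination can be criticised as it stands.

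**A reader might infer that the false-positive rate of this trial simply is 8-10%.** The documents do not support that. The inflation arises only if either time point suffices, and no section says so. If both are required, the error is at most 5%. Even on the either-suffices reading, a correlation above about 0.75 takes the figure below 8%, and zero correlation is implausible with the same patients measured twice. The figures are also two-sided; the superiority claim concerns one direction, with about half the error.

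**A reader might infer that requiring both would cost the planned power**, since 0.80² = 0.64 at zero correlation. The planned numbers do not bear this out if the difference is 25 percentage points. With 63/126 evaluable and control rates of 20-45%, power per time point is 91-94%. Joint power then runs from 0.908² = 82% at correlation 0 to 91% at correlation 0.8, above 80% throughout.

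**A reader might see a contradiction between the singular and plural wording.** There is none of substance. The abstract attaches both time points to its one endpoint, and Study objectives names no time point.

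**Conclusion.** The point holds in conditional form. The article sets up two full-alpha primary tests and does not say what counts as success. On the either-suffices reading the two-sided error is about 7-10% for assumed correlations of 0.9 down to 0, and a false claim favouring telemonitoring has a probability of about 3.5-4.9% against 2.5%. On the both-required reading there is no inflation. The error figures rest on the normal approximation and the assumed correlations. The power figures rest in addition on reading the planned difference as percentage points, which the Sample size section does not confirm.

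**What to change.** Before the comparative analysis, add one sentence to Primary outcome measures and to Planned statistical analyses that holds the overall two-sided error at 0.05. Two options:

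1. **Fixed order.** Test the two time points in a pre-stated order, each at 0.05, the second only if the first is significant. The sponsor chooses the order. The text does not dictate it, although an objective framed over 48 weeks may favour week 48 first. Cost: if the first test fails, the second time point cannot be claimed.
2. **Split.** Test each time point at 0.025. The error is then at most 5% (4.94% at correlation 0). Cost: with 63/126 evaluable, power per time point falls from at least about 91% to at least about 85%, provided the difference is 25 percentage points.

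The Sample size section should also say which test and time point it refers to, and whether the 25% is absolute or relative, because the cost of the split cannot be judged without that.

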#### Secondary outcome measures

A series of psychological and clinical variables will be used as secondary endpoints.

Scoring of the different psychological questionnaires will be computed for the HBPT and CM groups and compared between groups. They will be used to quantify therapeutic adherence, and compared with evaluation of compliance based on the patient’s report.

The following clinical endpoints will also be evaluated: (1) the percentage of patients with office blood pressure normalization (<140/90 mmHg) after 24 and 48 weeks; (2) percentage of patients with home blood pressure normalization (average <135/85 mmHg) after 24 and 48 weeks in the HBPT group; (3) changes in average 24-h systolic and diastolic blood pressure after 24 and 48 weeks *vs*. baseline; (4) changes in office systolic and diastolic blood pressure after 24 and 48 weeks *vs*. baseline; (5) changes in average home systolic and diastolic blood pressure after 24 and 48 weeks *vs*. baseline in the HBPT group; (6) the number of antihypertensive drugs prescribed after 24 and 48 weeks *vs*. baseline; (7) the number of office or phone visits after 24 and 48 weeks *vs*. baseline; (8) direct costs of patient management, based on additional medical visits and laboratory tests performed between baseline and 24 and 48 weeks; (9) adherence to treatment, as reported by the patient (the assessment of adherence and persistence to therapy will also be done indirectly, by evaluating adherence to the home blood pressure monitoring program and by evaluation of the psychological tests); (10) difference in target organ damage score between baseline and week 24 and 48 of the study; (11) difference in cardiovascular risk level between baseline and week 24 and 48 of the study according to Heart Score (ESH-ESC) and Framingham algorithm
[40,41]; (12) difference in the rate of cardiovascular events between baseline and 24 and 48 weeks of follow-up; and (13) the number of subjects showing regression of metabolic syndrome after 24 and 48 weeks from the randomization.

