Secondarily, the trial will investigate and compare between randomization groups personality traits predictive of adherence. This will be useful to identify possible psychological determinants of adherence to antihypertensive treatment, also relating them to blood pressure response to antihypertensive treatment in daily life conditions. Poor adherence to treatment remains one of the major limitations in the management of hypertension: it may cause poor blood pressure control and may contribute to increased morbidity, mortality, and costs
[45,46].

Previous studies have shown that persistence with antihypertensive therapy decreases with time: discontinuation rates vary from 22% to 50% of patients during the first year after treatment initiation
[47-50]. Therefore, improving adherence to treatment remains a major challenge for the treating physician. Use of blood pressure telemonitoring technique, which might help in improving blood pressure control and adherence, together with quantification and definition of the psychological trait of the hypertensive patient, might help identifying features of high-risk hypertensive patients and increase the chance of successful treatment.

The study will also evaluate the impact of HBPT on additional medical and economic outcomes, which might help in unmasking possible additional advantages of this technique in high-risk hypertensive patients, on a relatively long-term follow-up.

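### The stated analysis of the psychological scores tests four baseline-only traits between arms and uses scores as a measure of adherence, so it does not estimate the determinants of adherence that the trial sets out to find

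*Protocol article*

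**What the plan says.** **The aims.** Study objectives in the protocol article states two psychological aims in one sentence: "The study will also assess the psychological determinants of adherence and persistence to drug therapy and the influence of HBPT on such psychological factors". The first is also in the article's title.

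**The instruments.** Study procedures and Psychological tests describe two sets. Set 1 (SF-36, PGWBI, BDI, LoC, SEI, IBQ, COPE) is given at Visits 2, 5 and 7 to study the psychological impact of telemonitoring. Set 2 (STAY, TDP, TAP, TCI) is there to explore personality traits behind adherence behaviour. For set 2, the psychologists "will also assess the following psychological dimensions only at Visit 2", which is the randomisation visit.

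**The analysis.** Secondary outcome measures says of all the questionnaires: "Scoring of the different psychological questionnaires will be computed for the HBPT and CM groups and compared between groups". The next sentence adds: "They will be used to quantify therapeutic adherence, and compared with evaluation of compliance based on the patient’s report". Item 9 of the clinical endpoints in that section takes up the second idea: "the assessment of adherence and persistence to therapy will also be done indirectly, by evaluating adherence to the home blood pressure monitoring program" and, in the words that follow, by the psychological tests. Planned statistical analyses names analysis of variance and the Mantel-Haenszel chi-square test for baseline comparisons, then says: "The same tests will be used to compare primary and secondary study endpoints between the CM and HBPT groups". Multivariate methods may be added if thought necessary, with no outcome or predictors named.

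**The Discussion** says that "the trial will investigate and compare between randomization groups personality traits predictive of adherence". It goes on to say that this should help identify determinants of adherence and relate them to blood pressure response.

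**The concern.** A determinant of adherence is an association, across patients, between a psychological score and later adherence. Neither stated use of the scores estimates one.

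A comparison of set 2 between arms sets two randomised groups side by side on traits recorded once, at randomisation. It can show only whether randomisation happened to balance them. Using scores to quantify adherence puts them on the outcome side of the question. A score cannot be both the measure of adherence and the factor that explains it.

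If the text is followed literally, the trial yields P values for null hypotheses that randomisation makes true and no estimate for an aim in its own title. An accidental trait difference could also be taken for a result.

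**Working it through.** The protocol gives no figure for this part of the plan, so there is none to reproduce. The check sets each aim against the stated analysis and then gives a sense of scale.

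**Aim against analysis**

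| Aim | Data collected | Stated analysis | Does it estimate the aim? |
|---|---|---|---|
| Influence of telemonitoring on psychological factors | Set 1 at Visits 2, 5, 7 | Between arms | Yes, at Visits 5 and 7 |
| Traits behind adherence | Set 2 at Visit 2; adherence at all visits | Between arms | No, it checks baseline balance only |
| Determinants of adherence, both sets | Visit 2 scores; adherence at all visits | Scores used to quantify adherence and compared with reported compliance | No, the scores become the outcome measure |

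As Psychological tests describes them, the instruments measure quality of life, wellbeing, depression, locus of control, self-esteem, illness perception, coping, anxiety and personality. None is described as measuring adherence. Set 2 is completed at the same visit at which untreated patients start therapy, so it cannot measure their later adherence.

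**Inputs.** From Sample size: 252 patients (84 control, 168 telemonitoring), 25% drop-out, two-sided 0.05, 80% power. Evaluable: 252 × 0.75 = 189, that is 84 × 0.75 = 63 and 168 × 0.75 = 126. Normal quantiles: 1.960 and 0.8416, sum 2.8016.

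**1. Chance findings in the four traits** (one score per instrument, independent tests, each at 0.05)

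1 − 0.95^4 = 1 − 0.8145 = 0.185, or 18.5%.

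**2. What the arm comparison can detect**

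Standardised difference = 2.8016 × √(1/n₁ + 1/n₂).
- 63 and 126: 2.8016 × 0.1543 = 0.43
- 84 and 168: 2.8016 × 0.1336 = 0.37

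For set 2, a difference of this size would be a baseline imbalance.

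**3. What a score-to-adherence analysis can detect** (Fisher z, one unadjusted test)

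r = tanh(2.8016 / √(n − 3)).
- n = 189: tanh(2.8016 / 13.638) = tanh(0.2054) = 0.203
- n = 252: tanh(2.8016 / 15.780) = tanh(0.1775) = 0.176

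**4. The price of many tests.** Sets 1 and 2 hold 7 + 4 = 11 instruments. Unadjusted and independent, 1 − 0.95^11 = 0.431. With a Bonferroni level of 0.05/11 = 0.00455, the quantile is 2.838, and at n = 189 r = tanh((2.838 + 0.8416) / 13.638) = tanh(0.2698) = 0.26.

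**The case against.** The strongest reply is that the article does link the scores to adherence. The sentence after the arm comparison sets them against reported compliance. The Discussion intends to identify determinants and relate them to blood pressure response. Its phrase about comparing predictive traits between randomised groups could mean asking whether predictors act differently by arm, which is a score-by-arm interaction. Multivariate methods are allowed. The article condenses a fuller protocol, so the model may be specified elsewhere.

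Much of this stands. A reader might infer that the scores are planned only as an arm comparison and that the aim therefore cannot be answered. The documents do not support either reading: a comparison with compliance is stated, and scores and adherence are collected in the same patients. A reader might also infer that set 1 cannot supply determinants because it is measured after adherence has begun. That fails too. Set 1 is also given at Visit 2, and its later arm comparison properly serves the second aim.

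The reply does not rescue the stated analysis. The sentence about compliance gives the scores the role of an adherence measure, and item 9 repeats it. The Discussion states an intention without an analysis, and its one comparative phrase is at best ambiguous. The multivariate clause is an optional addition to the univariate tests. The point is also more than missing detail: the article states an analysis for these scores, and it does not suit the aim. An analysis plan that followed the text would inherit the problem, and one that did not would depart from the published protocol.

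**Conclusion.** The concern holds in this form: the analysis as stated does not estimate the determinants of adherence, while the planned data could. For the four Visit-2-only traits, the arm comparison is uninformative about adherence.

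The 18.5% assumes one score per instrument and independent tests. Subscales would raise it and correlation between instruments would change it, so it is an illustration. The detectable correlation of about 0.20 (189 patients) or 0.18 (252) is for a single unadjusted test; under Bonferroni over 11 instruments it is about 0.26 with 189. No power is claimed for interactions. Calling a trait difference chance assumes that answers are not affected by knowing the allocation. The article does not give the order of events within Visit 2, but a difference arising that way would say nothing about adherence either.

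This is a secondary aim and the primary blood pressure comparison is untouched. Because the aim is in the title and the correction is cheap, it should be made.

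**What to change.** In Secondary outcome measures:

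1. Drop the between-arm tests of STAY, TDP, TAP and TCI; describe these scores by arm at baseline.
2. Drop the use of psychological scores to quantify adherence, there and in item 9.
3. State that each Visit 2 score (sets 1 and 2) is a predictor of adherence over follow-up in a regression adjusted for arm. The outcome is the pill-count percentage already defined in Study procedures, with patient-reported adherence as a second measure. Add a score-by-arm interaction as exploratory.
4. Use the same model for blood pressure response, as the Discussion intends.
5. Keep the between-arm comparison of set 1 at Visits 5 and 7, for the influence of telemonitoring on psychological factors.
6. Label the regressions exploratory, or name a multiplicity correction.

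Reword the Discussion sentence on comparing traits between groups to match.

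The cost is wording and some regression models on data already being collected; no visits or patients are added. The drawbacks are that the associations are observational and must be reported so, and that there are many of them: 11 instruments, more with subscales, on more than one outcome.
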